**List of Abbreviations**

| **ARV** | **Actual resection volume** |
| --- | --- |
| **ARR** | **Actual resection ratio** |
| **DB** | **Blue Dye** |
| **BCS** | **Breast Conserving surgery** |
| **CDCG** | **Clavien Dindo Complication Grade** |
| **CCI** | **Comprehensive Complication Index** |
| **CRF** | **Case Report Form** |
| **DCIS** | **Ductal Cancer In Situ** |
| **FNA** | **Fine Needle Aspiration** |
| **MRI** | **Magnetic Resonance Imaging** |
| **ORV** | **Optimal Resection Volume** |
| **PREMs** | **Patient Reported Experience Measures** |
| **PROs** | **Patient Reported Outcomes** |
| **QoL** | **Quality of Life** |
| **RCT** | **Randomized Controlled Trial** |
| **RFID** | **Radiofrequency identification** |
| **RI** | **Radioisotope** |
| **RSL** | **Radioactive seed localization** |
| **SLN** | **Sentinel Lymph Node** |
| **SLND** | **Sentinel Lymph Node Dissection** |
| **SPIO** | **Superparamagnetic iron oxide nanoparticles** |
| **VAB** | **Vacuum Assisted Biopsy** |

|  |  |
| --- | --- |
| **Summary** |  |
| Title | Magnetic marker or guidewire localization of non-palpable breast cancer in combination with magnetic sentinel lymph node dissection. An open- label, phase 3, pragmati,crandomizedd controlled trial. |
| Clinical Relevance/Background | Preoperative tumour localisation for non- palpable breast cancer lesions has been traditionally performed with a Guidewire. This method is widely available, inexpensive and most of the radiologists and surgeons are familiar with it. However, drawbacks of this technique, including risk of migration, patient discomfort and logistical challenges have led to the development of alternative localisation methods, including magnetic seeds. Previous large cohorts have showed favourable outcomes of magnetic seed localisation, however this has not been investigated in a randomized trial. Furthermore the combination of a totally magnetic technique for lesion localisation and sentinel lymph node detection has not been examined. |
| Objectives | Primary:   - To examine how a magnetic marker compares to the guidewire in successful lesion localisation, minimal excess tissue removal and negative margins in surgery of non-palpable breast lesions. - To evaluate the combination of a ferromagnetic marker for tumour localisation with Superparamagnetic Iron Oxide Nanoparticle (SPIO) for sentinel lymph node detection (SLND) in early breast cancer treatment.   Secondary:   - To evaluate operative times and logistical efficacy of magnetic markers compared to guidewire in the above setting. - To evaluate patient as well as physician satisfaction with the use of this totally magnetic technique. - To evaluate patient quality of life (QoL) |
| Study Design and Methods | Multicentre Pragmatic Randomized Controlled Trial: Patients with confirmed non-palpable ductal cancer in situ (DCIS) or invasive breast cancer, planned for breast conserving surgery (BCS) and SLND will be randomized in two arms.  Arm 1: Lesion localisation with magnetic marker  Arm 2: Lesion localisation with guidewire  Axillary mapping will be done in both arms with the use of SPIO (1-1.5ml Magtrace ©, Endomag, Cambridge,UK) . In the interest of a pragmatic trial, lesion localisation with a magnetic marker as well as SPIO injection will be performed by either a breast surgeron or a radiologist and within a 14 day window before the operation according to local routines or case-per-case convenience. SPIO will be administered peritumoraly. Guidewire localisation will always be performed by a breast radiologist on the day or at most one day before surgery. All cases of localisation will be performed under local anesthetic.  The performing surgeon will document all relevant data in a case reporting form.  All patients will be followed up for postoperative complications, need for re-excision and QoL assessment for 2 years. QoL assessment will be done via PROs questionnaires and the patients experience will be evaluated with PREMs questionnaires.  All involved disciplines (surgeons, radiologists, co-ordinators) will rate their experience with each technique with Likert scale items. |
| Primary Endpoints | To examine the equivalence of magnetic marker and guidewire in successful localisation of non-palpable breast lesions by comparing:   - Re-excision rate - Resection ratio - Sentinel node detection rate |
| Secondary Endpoints | - Adverse events - Operative time - PROs and QoL evaluation - PREMs and cost- effectives analysis |
| Statistical Analysis Plan | A pragmatic randomized open label study to investigate the equivalence of a magnetic marker localisation to guidewire localisation of non-palpable breast lesions. |
| Patient Population | Patients with biopsy confirmed non-palpable breast malignancies planned for BCS and SLND. |
| Study Duration | 5 years |
| Inclusion Criteria | -Patients aged ≥ 18 years  -Patients with ductal cancer in situ (DCIS) or invasive breast cancer (T1-T3) requiring  localisation planned for primary surgery including sentinel node  biopsy. |
| Exclusion Criteria | -Intolerance / hypersensitivity to iron or dextran compounds or  Sienna XP  -Patients with iron-overload disease.  -Patients with pacemakers or other implantable devices in the  chest-wall, or prosthesis in the shoulder.  -Patients deprived of liberty or under guardianship.  -Pregnant or lactating patients.  -Inability to provide informed consent. |

**1.Background**

**1.1 Surgical treatment of Non-palpable Breast Cancer**

Breast cancer is the most commonly diagnosed noncutaneous malignancy in women. Its incidence has increased by an average of 0.4% each year, according to the Surveillance, Epidemiology, and End Results Program (SEER) database^1^. The refinement and wide implementation of screening programs as well as improvements in breast imaging have led to increased diagnosis of breast cancer at a pre-symptomatic stage, that is, non-palpable tumors and clinically negative axilla^2^. Breast-conserving surgery (BCS) is increasingly preferred by this patient group, given that when combined with radiotherapy, it confers equal oncological outcomes to mastectomy while ensuring better QoL ^3–5^. Simultaneously, axillary management has evolved from routine axillary clearance to sentinel node dissection (SLND), which is currently the standard treatment for clinically negative axilla^6^.

**1.2 Preoperative Lesion Localization**

The principle of breast-conserving surgery is twofold and comprises tumor excision with adequate margins, whereas healthy breast parenchyma is spared to ensure optimal cosmetic and functional outcomes. Accurate preoperative lesion localization is essential for achieving this.

**1.2.1 Guidewire Localization**

Since its introduction in the late 1970s, the guidewire has been the standard of care for breast lesion localisation ^7^. It is an inexpensive and widely available method with which most radiologists and surgeons are familiar.

However, various complications have been reported, including wire transection and retention of wire fragments in the breast or migration with damage to the surrounding structures ^8–10^. Furthermore, patient discomfort and pain render this method less appealing.

One of the most apparent disadvantages of this technique is the logistical challenge that it poses in theatre planning. A guidewire has to be inserted on the day of the surgery, which makes operation planning rather copious and may cause delays that not only affect the workload of radiologists and surgeons, but also pose a financial burden on the healthcare system.

**1.2.2 Non-Wire Localization Methods**

The aforementioned drawbacks of the guidewire technique have led to the development of novel methods that primarily aim to detach the preoperative localization from the operation day.

One of the first non-wire markers introduced in the early 2000s was radioactive seed localization (RSL), which uses ^125^I seeds for lesion localization, with many studies confirming favorable outcomes for guidewire localization^11,12^.

The strict regulations and technical difficulties that surround the use of radioactive seeds led to the development of non-radioactive markers such as radiofrequency (RFID) tags ^13,14^, radar reflectors ^15,16^ and magnetic seeds ^17–19^.

All wireless methods, despite the technology that they employ, are based on decoupling lesion localisation from surgery and facilitate theatre logistics.

**1.2.3 Ferromagnetic Seeds**

The Magseed © (Endomag, Cambridge, UK) magnetic marker system comprises a ferromagnetic marker and an 18 gauge needle delivery system used to deliver the marker to the intended deployment location. The stainless-steel marker is magnetically detectable but does not magnetically attract other metallic objects. The product was designed as a single-use device that is sterile in an individually sealed tyvek pouch. The Magseed© magnetic marker is 5mm long and has a diameter of 0.9mm. It is deployed under either ultrasound (US) or mammography guidance. The needle delivery system and markers are visible under both modalities. Magseed© is not suitable for MRI-guided deployment because the needle delivery system is not MRI-compatible. Using the delivery system, the marker is placed percutaneously in the breast for up to 30 days before surgery. A postplacement mammogram can be used to confirm that the marker is in the desired position in the breast.

During surgery, the marker facilitates magnetic localization of the target lesion using a SentiMag© (Endomag, Cambridge,UK) probe. Initially, the probe facilitated the identification of the approximate location of the marker before incision placement. After incision and within the surgical site, the probe was used to detect and localize the lesion for excision. For some lesions, the position of the incision can be determined by other means such as a skin mark.

The SentiMag© probe generates an alternating magnetic field that temporarily magnetizes the marker. The magnetic signature generated by the marker is then detected by a sensitive magnetometer in the probe. The unit displays a numerical reading and emits an audible tone that increases in frequency (pitch) with the marker's proximity to the probe. Once the marker has been localized, it is excised with the lesion.

[figure not shown]

[figure not shown]

[figure not shown]

Needle delivery System Ferromagnetic Seed Sentimag© probe

**1.3 Sentinel Lymph Node Detection with Superparamagnetic iron oxide nanoparticles**

Traditionally, axillary mapping and sentinel lymph node (SLN) detection have been performed using radioisotope (RI) with or without blue dye (BD)^20^. Although highly reliable, this combination poses challenges due to restricted access to nuclear medicine facilities and strict regulations, whereas the short half-life of RI and the allergenic reactions of BD limit its administration on the day of surgery, complicating logistics.

Superparamagnetic iron oxide nanoparticles (SPIO) are iron oxide nanoparticles covered in an organic coating that become transiently magnetic in the vicinity of a magnetic source. Magtrace ^©^ (Endomag, Cambridge, UK) is a liquid suspension of carboxydextran-coated iron oxide nanoparticles in injectable water. Each milliliter of Magtrace ^©^ contains approximately 28 mg of iron. SPIO has shown comparable performance to RI ± BD with the additional advantage of a wider timeframe for preoperative administration^21–23^. The perceived drawbacks of this method include skin staining and artifacts on postoperative magnetic resonance imaging (MRI) ^24^.

**1.4 The “MAGnetic marker To deTect primary Lesion and sentinel node in breast cancer” (MAGtotal) concept.**

The combined technique involves seed placement on the ventral surface of the tumor, while SPIO is injected dorsally to the tumor between the tumor and the chest-wall. Thus, we can achieve an enhanced signal that facilitates tumor localization, even in deeper lesions and larger breasts. Simultaneously, this technique is expected to minimize the risk of intraoperative confusion due to overlapping signals, which could lead to excision of larger specimens. Another concern that is addressed when SPIO is administered dorsally to the tumor is that the bulk of the brown-colored suspension is concentrated deep in the breast tissue and between the tumor and pectoral fascia, minimizing the risk of skin staining. The MAGtotal technique was tested in a pilot study with 32 patients with encouraging results that led to the design of a phase 3 RCT (100% clear margins, 1.49 resection ratio, 100% SLN detection)^25^.

**The Magtotal concept**

**
[figure not shown]
**

**2.Investigational Plan**

**2.1 Title**

Magnetic marker or guidewire localization of non-palpable breast cancer in combination with magnetic sentinel lymph node dissection. An open-label, phase 3, pragmatic, randomized controlled trial.

**2.2 Objectives**

**2.2.1 Primary Objective**

1. The primary objective is a composite of the three components of successful breast conserving surgery for early breast cancer. These components include the re-excision rate, minimal excess tissue removal, and successful SLN detection. The aim of this trial is to compare these three variables between the two arms.

The hypotheses to be tested are:

1. Magnetic marker lesion localization is not equivalent to guidewire localization in terms of re-excision rates due to inadequate surgical margins. Adequate margins are considered “no tumour on ink” for invasive cancer and 2 mm for pure DCIS and will be assessed by specialized breast pathologists.

2. Magnetic marker lesion localization is not equivalent to guidewire localization in terms of excess tissue removal. This will be expressed as the resection ratio and will be assessed by the ratio of the Optimal Resection Ratio (ORV) to the Actual Resection Ratio (ARV).

- ORV will be calculated for each tumour based on the radiological dimensions of the tumor (in cases of discordance between different modalities, the largest dimension will be used) using the volume calculation formula for ellipsoid tumours
[figure not shown]
, where *r*1= x radius +1cm, *r*2=y radius+1cm, *r*3= y radius +1cm. In all dimensions, 1 cm is added as it is the universally accepted macroscopic margin for breast lesions^26^.

ARV will be calculated based on the specimen weight.

Optimally, the ratio $\frac{ARV}{ORV}$ should be as close to 1 as possible to ensure that no unnecessary tissue is removed which may jeopardize the cosmetic and functional outcomes of a breast conserving operation.

3. The combination of magnetic markers and SPIO is not equivalent to the combination of a guidewire and SPIO for SLN detection.

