**2.6 Sampling and Data Analysis Plan**

The sample size is calculated based on the principle of equivalence, allowing for the detection of a significant difference in resection ratios of 0.3 adjusted for a non-inferiority margin of 4% for re-excision rates and SLN detection. The literature suggests a resection ratio for the guidewire between 2-2.8. To obtain robust results, we lowered that to 1.8 and accepted a 1.5 resection ratio for the totally magnetic technique stemming from our previous pilot study ^25^. Two-sided p-value is set at 0.05 and power to 80%. An additional 10% to sample size calculation will be recruited as inflation to pragmatic settings and tolerance.

The participants will be randomized with an allocation ratio of 1:1 in blocks of 8. The R-Randomizer package will be used for the randomization. The allocated arms will be in dark envelopes, and neither of the involved disciplines will be able to know the arm in which the participants will be randomized beforehand. All participants will receive a code upon randomization consisting of the first three letters of the recruiting center and a number that will be consecutive. The data will be collected by appointed research coordinators.

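### The primary objective is labelled a composite but posed as three separate hypotheses with no success rule, so the single 0.05 and single 80% cannot be attached to the trial's conclusion

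*Protocol*

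**What the plan says.** Section 2.2.1 opens with "The primary objective is a composite of the three components of successful breast conserving surgery for early breast cancer". It then says "The aim of this trial is to compare these three variables between the two arms" and sets out three hypotheses:

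1. "Magnetic marker lesion localization is not equivalent to guidewire localization in terms of re-excision rates due to inadequate surgical margins"
2. "Magnetic marker lesion localization is not equivalent to guidewire localization in terms of excess tissue removal"
3. "The combination of magnetic markers and SPIO is not equivalent to the combination of a guidewire and SPIO for SLN detection"

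The Primary Endpoints row of the Summary introduces the same three measures as separate items, under the words "To examine the equivalence of magnetic marker and guidewire in successful localisation of non-palpable breast lesions by comparing".

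Section 2.6 bases the sample size on equivalence, "allowing for the detection of a significant difference in resection ratios of 0.3", and adds a 4% non-inferiority margin for re-excision and sentinel node detection. The assumed mean ratios are 1.8 (guidewire) and 1.5 (magnetic). The error rate and power appear once: "Two-sided p-value is set at 0.05 and power to 80" per cent. The section gives no SD for the ratio, no control rate for re-excision or node detection, and no N.

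**The concern.** The label and the hypotheses point to different trials. A composite would be one outcome per patient and one test. Three hypotheses need a rule that turns three results into one conclusion. The protocol supplies neither, so 0.05 and 80% have no stated target.

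This matters because the trial is open-label and its endpoints differ in kind: one is continuous and two are proportions. As written, a favourable resection ratio alone could be presented as success while non-inferiority on re-excision is unproven. Equally, if one component failed, nobody could say from the protocol whether the trial had failed.

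**Working it through.** **Can the plan's own figures be reproduced?** No. With no N, SD or control rates, neither a sample size nor the 80% can be derived. What can be checked is what the stated levels would mean under each possible success rule.

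**Inputs from the protocol:** three hypotheses (2.2.1); two-sided 0.05, 80% power, ratio difference 1.8 − 1.5 = 0.3, margin 4% (2.6).

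**Rule A: any one endpoint suffices.** Family-wise error when all three null hypotheses are true and the tests are independent:
- each at 0.05: 1 − 0.95³ = 14.3% (upper bound under any dependence 3 × 0.05 = 15%);
- ratio at 0.05, two non-inferiority tests at one-sided 0.025: 1 − 0.95 × 0.975² = 9.7% (bound 10%);
- all three at one-sided 0.025: 1 − 0.975³ = 7.3% (bound 7.5%).

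Power is not the problem here. With 80% for each test, the chance of at least one success is 1 − 0.2³ = 99.2% under independence, and never below 80%.

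**Rule B: all three required.** The error rate stays at or below 0.05 with no adjustment. If each test had exactly 80% power, joint power would be:
- independent tests: 0.8³ = 51.2%;
- equal correlation 0.5 between test statistics: 61%;
- equal correlation 0.8: 69%;
- lowest possible under any dependence: 3 × 0.8 − 2 = 40%.

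**Rule C: one patient-level composite.** Neither figure applies. No composite rate, effect or margin is given, and no cut-off would turn the continuous ratio into success or failure for a patient.

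**How far Rule B depends on N.** The following inputs are assumptions, not protocol figures: SD of the ratio 1.0, node detection failure 2%, re-excision 5% or 10%, no true difference in the two proportions, independent tests, non-inferiority at one-sided 0.025.

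With k = (1.960 + 0.842)² ≈ 7.849, the number per arm for 80% power is:
- ratio: 2k·SD²/0.3² = 175 (112 at SD 0.8; 393 at SD 1.5);
- non-inferiority: 2k·p(1 − p)/0.04² = 193 at p = 2%, 467 at 5%, 883 at 10%.

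Power at each possible size is Φ(0.3/√(2·SD²/n) − 1.96) for the ratio and Φ(0.04/√(2p(1 − p)/n) − 1.96) for each proportion:

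| n per arm | Set by | Ratio | Node detection | Re-excision | Joint |
|---|---|---|---|---|---|
| 175 | ratio | 80% | 76% | 40% (at 5%) | 0.80 × 0.762 × 0.404 = 25% |
| 175 | ratio | 80% | 76% | 24% (at 10%) | 0.80 × 0.762 × 0.238 = 15% |
| 467 | re-excision at 5% | 99.6% | 99.2% | 80% | 79% |
| 883 | re-excision at 10% | >99.9% | >99.9% | 80% | 80% |

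So the same 80% is compatible with a joint power anywhere from about 15% to 80%, depending on which endpoint set N. The protocol does not say which did.

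**The case against.** The strongest reply is that the text leans towards requiring all three. The label suggests components that belong together, and section 4 expects logistical gains without loss of oncological or cosmetic outcome. On that reading there is no alpha inflation. Section 2.6 can also be read as sizing the ratio and then adjusting for the 4% margin, which is compatible with N being set by the most demanding endpoint. The 0.05 is stated once, in the sample-size paragraph, and nowhere does the protocol say that each hypothesis is tested at that level. Finally, a multiplicity procedure is often left to the SAP, which is not shown.

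Much of this stands. A reader might infer three stronger things that the document does not support:

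- **That both 0.05 and 80% are wrong whatever the rule.** Under an all-three rule 0.05 remains valid. Under an any-one rule 80% remains a lower bound, provided at least one test has it.
- **That one 80% cannot hold for all three endpoints.** It can, as a minimum, if the most demanding endpoint sets N.
- **That the trial has only about a 50% chance, or a 15–25% chance, of meeting its objective.** Those figures need either exactly 80% on every test or an N set by the ratio alone. The protocol states neither.

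The absence of a multiplicity method is likewise not the point. What remains is the protocol's own text: a label that conflicts with the hypotheses below it, and an error rate and power with no stated target. What the primary objective is, and what the sample size is powered for, belong in the protocol.

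**Conclusion.** The point holds as one of undefined meaning, not of a proven error in either number. The protocol does not fix what counts as success, so its 0.05 and 80% cannot be attached to the overall conclusion.

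- If any one endpoint suffices, the error rate is about 14% with each test at 0.05, or 7–10% with one-sided 0.025 for non-inferiority. These figures assume independence and all nulls true.
- If all three are required, the error rate is sound and joint power is unknown. It is 51% with exactly 80% on each independent test, and 79–80% if re-excision set N on the assumed inputs.

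The 14% and 51% use only the stated levels plus independence. Everything that involves a number per arm rests on the assumed SD and event rates.

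**What to change.** **Section 2.2.1 and the Summary.** Replace the composite label with three co-primary endpoints. State that overall success is declared only if all three are met, each at two-sided 0.05 (one-sided 0.025 for a non-inferiority test), with no split of alpha.

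A testing order adds nothing to that overall verdict. If claims on single endpoints are also wanted, test in a fixed order (re-excision, node detection, resection ratio) and stop at the first failure.

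The amendment in section 8 is dated April 2020, and the reference list includes a December 2022 publication. The change should therefore record that the rule was fixed before any outcome data by arm were seen.

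**Section 2.6.** Reconcile the equivalence wording, which also appears in the Summary and in the hypotheses, with the 4% non-inferiority margin and the 0.3 difference. In particular, say whether the ratio is tested for equivalence or for a difference. If 0.3 were meant as an equivalence margin, the assumed means of 1.8 and 1.5 would lie exactly on it. Give the SD, the control rates and the N used, and restate power for each endpoint and jointly.

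**Cost.** Protocol wording and a recalculation. The power quoted may turn out less favourable than 80%. No patients need be added unless the sponsor chooses to raise joint power.

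### As printed, the ORV formula uses the y radius for both the second and third semi-axes, so the tumour's third dimension never enters the denominator of a primary endpoint

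*Protocol*

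**What the plan says.** Section 2.2.1 of the protocol states that "ORV will be calculated for each tumour based on the radiological dimensions of the tumor", "using the volume calculation formula for ellipsoid tumours". The formula is an image that is not shown, but the semi-axes are defined in readable text. The first is "r*1= x radius +1cm" and the other two are "r*2=y radius+1cm, *r*3= y radius +1cm". The paragraph continues: "In all dimensions, 1 cm is added".

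The only rule on choosing a measurement is that "in cases of discordance between different modalities, the largest dimension will be used". It settles disagreement between imaging methods. It does not say which diameter is x and which is y.

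The endpoint is ARV/ORV, which "should be as close to 1 as possible to ensure that no unnecessary tissue is removed". The Summary lists the resection ratio among the three primary endpoints, and section 2.6 plans on 1.8 for guidewire against 1.5 for the magnetic technique.

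**The concern.** An ellipsoid has three semi-axes, and the text names three (r1, r2, r3), yet r2 and r3 are the same quantity. No z radius is defined, and no spheroid or two-diameter convention is stated that would explain repeating y. The definition therefore conflicts with the paragraph's own statement about all dimensions.

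ORV divides the specimen volume, so any error in it passes straight into the resection ratio. In a multicentre trial, one site may follow the text literally while another silently uses three diameters. Their ratios would then not be comparable. Section 3.2 lists radiographic tumour size and ORV as data items but does not say that three diameters are kept, so later recalculation is not assured.

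**Working it through.** **Inputs**
- Semi-axes: section 2.2.1, as quoted above, with each radius taken as half the diameter.
- Volume: assumed V = 4/3·π·r1·r2·r3, because the formula image is not shown.
- Ratio: ARV/ORV. One sentence in section 2.2.1 words the ratio the other way round. The displayed fraction and the values 1.49 (section 1.4), 1.5 and 1.8 (section 2.6) fit ARV/ORV.
- Tumour diameters: all assumed. The protocol gives none, and section 2.3.1 admits T1 to T3. It contains no worked ORV, so there is no figure to reproduce.

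**Step 1: size of the error.** Dividing the printed volume by the three-axis volume, r1 and r2 cancel:

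ORV(printed)/ORV(three-axis) = (y radius + 1)/(z radius + 1)

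This equals 1 only when y = z. The recorded ratio is the three-axis ratio divided by this factor.

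**Step 2: one tumour, three labellings.** Take diameters of 10, 10 and 20 mm. With the margin, the semi-axes are 1.5, 1.5 and 2.0 cm. The three-axis ORV is 4/3·π·1.5·1.5·2.0 = 18.85 cm3 under any labelling.

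| Long diameter called | Printed r1, r2, r3 (cm) | Printed ORV (cm3) | Factor | A ratio of 1.5 is recorded as |
|---|---|---|---|---|
| x | 2.0, 1.5, 1.5 | 18.85 | 1.00 | 1.50 |
| z | 1.5, 1.5, 1.5 | 14.14 | 0.75 | 2.00 |
| y | 1.5, 2.0, 2.0 | 25.13 | 1.33 | 1.13 |

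**Step 3: other assumed shapes** (x × y × z, cm).
- 2 × 1.5 × 1: printed 25.66 against 21.99 cm3, factor 1.17; 1.5 is recorded as 1.29.
- 4 × 3 × 1.5: printed 78.54 against 54.98 cm3, factor 1.43; 1.5 is recorded as 1.05.
- 5 × 2 × 4: printed 58.64 against 87.96 cm3, factor 0.67; 1.5 is recorded as 2.25.
- 5 × 4 × 2: printed 131.95 against 87.96 cm3, factor 1.50; 1.5 is recorded as 1.00.
- 1.5 × 1 × 1: both 16.49 cm3, no error.

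**Step 4: if two diameters were intended.** For a 3 × 2 cm lesion, x = 3 and y = 2 gives 4/3·π·2.5·2·2 = 41.89 cm3. Swapping the labels gives 4/3·π·2·2.5·2.5 = 52.36 cm3. A specimen that scores 1.5 under the first labelling scores 1.5 × 41.89/52.36 = 1.20 under the second.

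**Step 5: effect on the arm comparison.** Suppose the factor f is unrelated to arm and to the three-axis ratio. For a common f, arm values of 1.8 and 1.5 become 1.8/f and 1.5/f. At f = 1.333 they are 1.35 and 1.125, a difference of 0.225. At f = 0.75 they are 2.40 and 2.00, a difference of 0.40. If the arms do not differ, they still do not differ. When f varies between patients, that variation is added to the spread of the ratio.

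**The case against.** The strongest reply is that this is a one-letter slip. The text names an ellipsoid, uses three symbols and refers to all dimensions, so most readers would take r3 as the z radius. Nothing shows that any site computes ORV with y twice. That is likely right, and it makes the correction easy. It does not make the printed definition usable, because that definition is the only rule given.

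A second reply is that repeating y gives a spheroid, a possible convention when only two diameters are available. The protocol states no such convention, and Step 4 shows that the result would still depend on labels it leaves undefined.

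Three stronger readings are tempting, and the document does not support them.
- **That unblinded staff choose the axes, so the error favours one arm.** The protocol does not say who assigns x and y or computes ORV, or whether this comes before or after allocation. Section 3.2 lists ORV as preoperative data, and section 2.6 conceals allocation in envelopes. The trial is open-label, so computation with knowledge of the arm is possible, but it is not stated. Fixing ORV before allocation is known would address a separate question that the repeated y does not raise.
- **That individual shifts larger than 0.3 swamp the planned effect.** The 0.3 in section 2.6 is a difference between arms, whereas the shifts above are per patient. Randomisation balances tumour shape in expectation, so they do not become an arm difference of that size.
- **That every elongated tumour is mis-scaled.** With the long diameter as x and the other two equal, the error is zero.

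**Conclusion.** The definition is wrong as written and should be corrected, because it sets the denominator of a primary endpoint. The error factor is (y radius + 1)/(z radius + 1). It ran from 0.67 to 1.50 over the assumed shapes and is 1 when y = z. The sure consequences of following the text are extra variance in the resection ratio and absolute values that cannot be read against 1, 1.5 or 1.8. A real arm difference would be rescaled, but none would be created, so there is no built-in bias towards either technique.

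The cost in power cannot be stated: the protocol gives neither a standard deviation for the ratio nor a distribution of tumour shapes. The volumes rest on the assumed 4/3·π formula and assumed diameters. The factor itself holds for any volume proportional to the product of the three semi-axes.

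**What to change.** In section 2.2.1, set r3 = z radius + 1 cm. If only two diameters are measured for some or all tumours, state one fixed rule for the third axis and one for which diameter is x and which is y. Apply both identically in both arms and at all sites. Record in the CRF the diameters actually used, so that every ORV, including any already computed, can be recalculated under the corrected rule.

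The cost is one formula correction and an added CRF field for the diameters.
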